# Oral Health Coaches at Well-Baby Clinics to Promote Oral Health in Preschool Children From the First Erupted Tooth: Protocol for a Multisite, Pragmatic Randomized Controlled Trial

**DOI:** 10.2196/39683

**Published:** 2022-08-31

**Keywords:** randomized clinical trial, dental caries, early childhood caries, oral health promotion, behavior change, motivational interviewing, dental public health, child health care, health inequality, prevention

## Abstract

**Background:**

Early childhood caries is considered one of the most prevalent diseases in childhood, affecting almost half of preschool-age children globally. In the Netherlands, approximately one-third of children aged 5 years already have dental caries, and dental care providers experience problems reaching out to these children.

**Objective:**

Within the proposed trial, we aim to test the hypothesis that, compared to children who receive usual care, children who receive the Toddler Oral Health Intervention as add-on care will have a reduced cumulative caries incidence and caries incidence density at the age of 48 months.

**Methods:**

This pragmatic, 2-arm, individually randomized controlled trial is being conducted in the Netherlands and has been approved by the Medical Ethics Research Board of University Medical Center Utrecht. Parents with children aged 6 to 12 months attending 1 of the 9 selected well-baby clinics are invited to participate. Only healthy children (ie, not requiring any form of specialized health care) with parents that have sufficient command of the Dutch language and have no plans to move outside the well-baby clinic region are eligible. Both groups receive conventional oral health education in well-baby clinics during regular well-baby clinic visits between the ages of 6 to 48 months. After concealed random allocation of interventions, the intervention group also receives the Toddler Oral Health Intervention from an oral health coach. The Toddler Oral Health Intervention combines behavioral interventions of proven effectiveness in caries prevention. Data are collected at baseline, at 24 months, and at 48 months. The primary study endpoint is cumulative caries incidence for children aged 48 months, and will be analyzed according to the intention-to-treat principle. For children aged 48 months, the balance between costs and effects of the Toddler Oral Health Intervention will be evaluated, and for children aged 24 months, the effects of the Toddler Oral Health Intervention on behavioral determinants, alongside cumulative caries incidence, will be compared.

**Results:**

The first parent-child dyads were enrolled in June 2017, and recruitment was finished in June 2019. We enrolled 402 parent-child dyads.

**Conclusions:**

All follow-up interventions and data collection will be completed by the end of 2022, and the trial results are expected soon thereafter. Results will be shared at international conferences and via peer-reviewed publication.

**Trial Registration:**

Netherlands Trial Register NL8737; https://trialsearch.who.int/Trial2.aspx?TrialID=NL8737

**International Registered Report Identifier (IRRID):**

DERR1-10.2196/39683

## Introduction

Dental caries (or tooth decay) represents a major public health problem affecting almost half of preschool-age children worldwide [1]. Early childhood caries (ECC) may have severe consequences on daily functioning and socialization in young children [2,3]. While dental caries is highly preventable with twice-daily toothbrushing using fluoridated toothpaste and limited sugar intake between main meals, compliance with these measures still requires much perseverance and endurance from parents. Noncompliance is often related to a lack of awareness among parents about their role in preventing ECC, a persistent belief that primary teeth are not important for oral health in later life, power struggles with the child, and tiredness of parents and their children [4-6]. As with many behavior-related diseases, dental caries shows marked socioeconomic disparities in all age groups [7,8].

Life-course epidemiology has highlighted that early childhood is critical for developing good oral health [9,10]. Positive oral hygiene behaviors and skills should be introduced early in the child’s life, and parents need to acquire the knowledge to develop proper oral hygiene behaviors and skills [10]. This knowledge about the importance of caries prevention in early childhood contributes to the recommendation to have an early dental visit before the age of 1 year [11]. However, while in the Netherlands parents’ compulsory health care insurance fully covers oral health care for their children up to the age of 18 years, oral health care professionals experience difficulties reaching children below 5 years of age, particularly those with lower socioeconomic backgrounds. As a result, less than half of Dutch children have visited an oral health professional at the age of 4 years, and dentin caries is present in about one-third of Dutch children aged 5 years [12,13]. At the same time, more than 90% of all newborns, including children from low socioeconomic backgrounds, visit well-baby clinics (WBCs) for preventive health care and vaccinations at regular intervals up to the age of 4 years [14]. Therefore, WBCs provide a unique window of opportunity for early oral health promotion.

Nevertheless, due to lack of time, medical and nursing staff at WBCs pay little attention to oral health promotion and timely referral to oral health professionals, prioritizing other child health issues over oral health promotion [15]. The second problem is that even when children visit an oral health professional on time, there is a lack of evidence-based interventions to provide appropriate preventive oral care starting from the first tooth [16]. Therefore, there is a double challenge in preventing poor oral health in early childhood. First, to reach young children with their parents in a timely fashion, and second, to develop and provide effective preventive oral health care and oral health promotion to address behavioral risk factors for poor oral health.

The Toddler Oral Health Intervention (TOHI; *Gezonde Peutermonden* in Dutch) has been developed to address these challenges by providing proven, effective early interventions. Firstly, in the TOHI, an oral health coach (OHC) is assigned by a dental clinic to participating WBCs in the same neighborhood. For children aged 6 to 12 months up to 48 months attending WBCs, the TOHI combines the regular WBC appointments with an appointment with the OHC. In doing so, the TOHI follows the example of the nationwide Scottish Childsmile program [17,18]. This program has successfully reached very young children and their parents through WBCs. Secondly, the OHC works according to the Non-Operative Caries Treatment And Prevention (NOCTP) approach, which has been reported to result in a 40% reduction in caries incidence in Dutch schoolchildren [19]. Thirdly, the OHC will use motivational interviewing (MI). While MI was initially developed as a behavioral technique for treating substance abuse [20], it has been shown to be effective in contributing to the prevention of ECC. MI has led to a reduction in caries incidence ranging from 16% to 26% and a 30% to 55% reduction in the number of decayed teeth [21-24]. Finally, the Health Action Process Approach (HAPA) [25], a theoretical framework to explain, predict, and modify health behaviors, provides tools to focus on the underlying determinants of behavior. By understanding the stages of behavioral change and focusing the intervention on the associated determinants, the impact of NOCTP and MI can be increased. The importance of determinants that underpin motivational and self-regulatory processes and help translate intention into behavior in oral health care, such as attitudes, self-efficacy, planning, and action control, has been demonstrated in previous research [26-29]. As the TOHI combines different existing components of health care and works on different organizational levels, it can be considered a complex intervention following the definition of the Medical Research Council (MRC) [30].

This paper describes a detailed research protocol to assess the effectiveness of the TOHI as an addition to usual WBC care, compared to usual WBC care only, in children aged up to 48 months. We hypothesize that the TOHI as an addition to usual care will reduce cumulative caries incidence at the age of 48 months (ie, the primary outcome measure), the sum of the number of decayed, missing, and filled surfaces and teeth (dmfs/dmft), the caries incidence density (person-time at risk to the first cavity), the presence of dental plaque, and the consequences of untreated caries (ie, secondary oral health outcome measures). We will study and report on (1) the oral health outcomes, (2) the behavioral outcomes, and (3) the balance between costs and effects of the TOHI.

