### Sample Size Calculation

Previous studies show that the average number of caries lesions in Dutch children at the age of 5 years is 4.5 (SD 4.5) [12]. This information was used for study size estimation using G*power 3 [34]. This showed that the intervention group needed at least 149 participants to demonstrate a reduction in cumulative caries incidence of at least 30% with a statistically significant Mann-Whitney *U* test allowing for statistical power (1-β) of .8 and a 2-sided α of .05 as a threshold for statistical significance. With an anticipated 30% loss to follow up, the aim was to include at least 200 participants per group.

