### Intervention Randomization

With a 1:1 ratio, participating parent-child dyads were individually allocated to the intervention or control group. This allocation of the TOHI as an add-on to usual care was stratified for each WBC (9 in total) and educational level of the mother (classed as low, medium, or high) as an indicator of SEP. A computerized random sequence generator [35] with a block size of 4 to ensure equally filled strata in each group was used to allocate the intervention status to predefined unique ID numbers. Accordingly, an intervention allocation file was prepared, including intervention codes with blocked series of ranked unique participant IDs for the strata.

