### Design of Data Analyses

All analyses of the effectiveness of the TOHI will make use of the intention-to-treat principle. To prevent biased principal data analysis, concealment will be maintained during data analysis. The blinding of the study comparison will be broken only after the completion of data analysis for the evaluation of outcomes for children at the age of 48 months. After data cleaning and prior to data analysis, the amount and patterns of missing data will be explored. Sensitivity analysis will be used to explore the impact of missing data. The 3 following scenarios will be assumed: stability over time (last value carried forward or backwards to replace missing value), best case (largest positive change score observed to replace missing value), and worst case (largest negative change score observed to replace missing value).

The intervention effects for the cumulative caries incidence at 48 months and the average dmfs/dmft will be compared as the risk difference (additive scale), numbers needed to treat, and the relative risk (multiplicative scale), all with the 95% CI. Effects for subgroups (ie, WBC, education level of the mother, and health literacy) will be evaluated with interaction terms in a multivariate regression analysis. To determine incidence density and person-time at risk, the median and mean between-group differences in caries incidence (or the person-time to first caries lesion) will be based on a Kaplan-Meier analysis and incidence differences and ratios. In addition, when applicable, Cox proportional hazard regression analysis will be applied to explore relations with independent variables. Between-group differences at the age of 24 months will be assessed for the secondary outcomes, notably changes in the behavioral determinants (defined according to the HAPA), plaque, and self-reported oral health behavior, using linear regression analysis. Results from all analyses will be presented with the 95% CI. For all analyses, the SEP stratum will be used as the primary covariable, while sociodemographic characteristics for which a baseline difference is observed will be used as secondary covariables. Such postrandomization differences between groups will be explored using descriptive statistics. A difference of 20% for discrete variables, a full standard deviation (pooled) for normally distributed data, and a quartile for nonnormally distributed data will be used as thresholds for similarity.

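### Clinic was a randomisation stratum but is not in the fixed covariate set (intervals slightly too wide if clinics differ); separately, coach clustering in the intervention arm merits a conditional sensitivity analysis

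*Protocol article*

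**What the plan says.** Under Intervention Randomization, children were individually allocated 1:1 and the allocation "was stratified for each WBC (9 in total) and educational level of the mother", in blocks of four. That is 9 clinics by 3 education levels.

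Under Design of Data Analyses, the primary effect is reported as a risk difference, number needed to treat and relative risk with 95% intervals. Kaplan-Meier, Cox and linear regression are named for other outcomes. On adjustment: "For all analyses, the SEP stratum will be used as the primary covariable". Sociodemographic characteristics that show a baseline difference are secondary covariables. Clinic is listed there only as one of three subgroup factors, to be examined through interaction terms.

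On delivery, the Introduction says "an oral health coach (OHC) is assigned by a dental clinic to participating WBCs in the same neighborhood". Procedures of the TOHI describes repeated face-to-face appointments with a coach from infancy to 42 months. The Interventions section gives the control group usual clinic care only. Nothing states how many coaches there are, whether a child keeps the same coach, or whether the coach's identity is recorded for each child. Neither the analysis section nor the Sample Size Calculation mentions a coach effect or a clustering allowance.

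**The concern.** There are two points, and they pull in opposite directions.

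**Clinic.** Stratifying by clinic balances the arms within each clinic, so clinic differences cancel out of the treatment contrast. An analysis without clinic still counts those differences as noise. The standard error is then larger than the sampling variation it describes, and some of the precision gained by stratifying is lost. The text fixes a covariate set for all analyses that takes one stratification factor and passes over the other.

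**Coach.** Only intervention children share a coach. If coaches differ in skill, outcomes within a caseload are correlated in that arm alone. A comparison that treats every child as independent then understates uncertainty for any statement about coaches in general. This matters because a superiority finding on the primary outcome also triggers the cost-effectiveness analysis.

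**Working it through.** **The plan's own figure.** No figure in the article covers clinic or coach effects. The nearest is the sample size: "the intervention group needed at least 149 participants", from "the average number of caries lesions in Dutch children at the age of 5 years is 4.5 (SD 4.5") and a 30% reduction. Applied to the mean, that is 0.30 × 4.5 = 1.35 lesions, or d = 1.35/4.5 = 0.30. At two-sided 0.05 and 80% power this gives 176 per arm by t-test and 184 by Mann-Whitney with a normal parent, so 149 was not reproduced. That is a separate matter and does not bear on this point.

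**Inputs**
- From the article: 402 randomised, 1:1, 30% anticipated loss. Evaluable per arm: 201 × 0.7 ≈ 141. Clinics: 9.
- Assumed, because not in the article: clinic ICC 0.05 and 0.10; coaches K = 5, 9, 15, 18; coach ICC ρ = 0 to 0.05; one coach per intervention child; equal caseloads.

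**Step 1: omitting clinic.** With arms balanced within clinics, the true variance of the contrast excludes the between-clinic part, but the unadjusted variance includes it. The unadjusted standard error is therefore too large by about 1/√(1 − ICC):
- ICC 0.05: 1/√0.95 = 1.026
- ICC 0.10: 1/√0.90 = 1.054

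Simulation (9 clinics, 149 per arm, continuous outcome, no coach effect, 20,000 runs):

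| Clinic ICC | Type I error, unadjusted | With clinic fixed effect |
|---|---|---|
| 0 | 5.0% | 5.0% |
| 0.05 | 4.7% | 5.2% |
| 0.10 | 4.0% | 5.0% |

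**Step 2: coach clustering in one arm.** With m = 141/K children per coach, DE = 1 + (m − 1)ρ applies to the intervention arm only. The ratio of true to naive standard error is √((1 + DE)/2), and type I error is 2[1 − Φ(1.96/ratio)].

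| K | m | ρ | DE | SE ratio | Type I error |
|---|---|---|---|---|---|
| any | – | 0 | 1.00 | 1.000 | 5.0% |
| 5 | 28.2 | 0.01 / 0.02 / 0.05 | 1.27 / 1.54 / 2.36 | 1.066 / 1.128 / 1.296 | 6.6 / 8.2 / 13.1% |
| 9 | 15.7 | 0.01 / 0.02 / 0.05 | 1.15 / 1.29 / 1.73 | 1.036 / 1.071 / 1.169 | 5.9 / 6.7 / 9.4% |
| 15 | 9.4 | 0.01 / 0.02 / 0.05 | 1.08 / 1.17 / 1.42 | 1.021 / 1.041 / 1.100 | 5.5 / 6.0 / 7.5% |
| 18 | 7.8 | 0.01 / 0.02 / 0.05 | 1.07 / 1.14 / 1.34 | 1.017 / 1.034 / 1.082 | 5.4 / 5.8 / 7.0% |

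Simulation at K = 9 (141 per arm, risk 33%, 8,000 runs) gave 5.9 / 6.7 / 9.5%. Using 149 per arm instead of 141 gives 5.9 / 6.8 / 9.6% for K = 9 and 5.5 / 6.0 / 7.6% for K = 15.

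**Step 3: does a clinic term deal with coaches?** No. At clinic ICC 0.05 and coach ICC 0.05, type I error was 9.2% unadjusted and 10.3% with a clinic fixed effect. A common clinic effect removes what both arms share; the coach effect sits in one arm.

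**Step 4: does a coach-clustered variance work with so few clusters?** With intervention children clustered by coach, controls as singletons and Satterthwaite degrees of freedom, simulated type I error was 4.8 to 5.4% with 9 coaches and 5.3 to 5.8% with 5. At K = 9 the mean interval width was 0.221 for the naive analysis. The clustered analysis gave 0.228 at ρ = 0 (0.228/0.221 = 1.03) and 0.238 / 0.246 / 0.272 at ρ = 0.01 / 0.02 / 0.05 (8, 11 and 23% wider).

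**The case against.** The strongest objections concern the coach point, and most of them stand.

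- **Missing inputs.** The article gives no number of coaches, caseloads or ICC, and does not say that a child keeps one coach. If children see several coaches, the simple design effect does not apply.
- **Coaches may differ little.** The trial uses a standardised risk protocol, uniform records, training every 3 to 4 months and feedback on recordings. Measuring coach fidelity does not show that caries outcomes vary by coach.
- **Which null hypothesis.** Children were individually randomised. If the intervention affects no child, or if inference is confined to these coaches, the ordinary comparison keeps its level. The inflated rates require coach effects that average zero but differ between coaches, and a conclusion meant for other coaches. The Discussion does aim to inform wider practice, so the broader inference is reasonable, but it is a choice.
- **Condensed article.** A coach term may be in a fuller plan. Independence is inferred from the methods named; it is not stated.

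A reader might infer that a handful of coaches makes the primary intervals definitely too narrow and the false-positive rate definitely above 5%. The article does not support that, since it rests on unstated inputs and on a choice of inference. A reader might also take the missing clinic term as a cause of narrow intervals; its effect is the reverse. Nor is it exact to say that the analysis uses only the SEP stratum: imbalanced variables may be added, and clinic is examined by interaction.

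The clinic point withstands these objections. The covariate set is written down for all analyses, so this is not mere silence, and a subgroup interaction analysis does not place clinic in the main-effect model.

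**Conclusion.** The clinic point holds as a small, definite mismatch between how the trial was randomised and the covariates fixed for its analysis. Its consequence is mild conservatism and some lost precision: standard errors about 3 to 5% too large at clinic ICC 0.05 to 0.10, and none if clinics do not differ. It does not threaten validity.

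The coach point holds only conditionally, and as a sensitivity analysis. It needs coaches who differ, children largely tied to one coach, and a conclusion meant to extend beyond these coaches. Given those, with 9 coaches and ICC 0.01 to 0.05, the true standard error is 4 to 17% larger than the naive one and type I error is about 6 to 9.5%. With 15 to 18 coaches type I error is about 5.4 to 7.6%; with 5 it is about 7 to 13%. At ICC 0 there is no error. All of these rest on assumed K and ICC.

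**What to change.** **Primary model.** Name clinic and maternal education together as covariates, since both defined the strata. Enter them as main effects: 9 × 3 = 27 separate strata would hold only about 282/27 ≈ 10 evaluable children each. The cost is 8 degrees of freedom for clinic. Keep the planned clinic interaction as a subgroup analysis.

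**Sensitivity analysis.** Where coach identity is available for each intervention child, pre-state an analysis with intervention children clustered by coach and controls as singletons (a partially nested model or coach-robust variance), with small-sample degrees of freedom. Report the number of coaches and the coach ICC. If children changed coach, state in advance how they are assigned. The cost is a somewhat wider interval: about 3% with 9 coaches if coaches do not differ, and 8 to 23% at ICC 0.01 to 0.05. If coach identity was not kept, say so and describe the primary interval as applying to the coaches in this trial.

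Both changes should be fixed before the allocation code is broken. Neither alters the trial's conduct.

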## Methods

### Trial Design and Setting

This protocol describes a pragmatic, 2-arm, individually randomized controlled trial (RCT) conducted in the Netherlands. The study population was recruited at 9 WBCs in urban and suburban regions with a population of predominantly low to middle socioeconomic position (SEP). Figure 1 shows a flow chart of the study’s overall design. This paper has been prepared following the Standard Protocol Items: Recommendations for Interventional Trials (SPIRIT) reporting guidelines [31] and the Template for Intervention Description and Replication (TIDieR) [32].

**Figure 1 figure1:**
[figure not shown]
Outline of the randomized controlled trial.

### Ethical Considerations

Prior to study initiation, the research protocol was submitted to the Medical Ethics Committee of the University Medical Centre Utrecht for review and approval. The committee provided ethics clearance (NL60021.041.17; file number 17-133/D) and stated that the research complied with the applicable rules and requirements of the Medical Research Involving Human Subjects Act (Dutch abbreviation: WMO) and with the ethics code for the conduct of research as set out in the national Code of Conduct for Scientific Integrity in the Netherlands [33]. Participation was voluntary, and participants could withdraw at any moment with no consequences. Participants signed an informed consent form before enrollment. The trial is registered in the Netherlands Trial Register (NL8737).

### Participants and Eligibility Criteria

This study includes parent-child dyads with children aged 6 to 12 months. The study excludes dyads with (1) children in need of specialized health care for a physical, mental, or medical condition; (2) parents with insufficient knowledge of Dutch; and (3) parents who expected to move outside the region of the WBC within the duration of the study. In the case of twins, only 1 child is enrolled in the study.

